### Randomization and Blinding

A randomization sequence will be created by an external researcher with Random Allocation software (Windows Inc) with a 1:1 allocation using random block sizes. The allocation sequence will be concealed from the external researcher enrolling participants in sequentially numbered, opaque, sealed, and stapled envelopes. Corresponding envelopes will be opened after assessment at baseline by another independent researcher, who will be responsible for advising participants of their allocation by telephone.

Assessors will be blinded to randomization until the end of the study. Owing to the nature of the trial, the researchers responsible for the intervention and the volunteers will not be blinded to randomization.

### Intervention

The intervention protocol follows all protective measures recommended in response to the COVID-19 pandemic. The intervention group (IG) will receive a remote case management intervention at home over 16 weeks, once a week by video or a telephone call. Volunteers who have regular access to the internet and a smartphone or computer made weekly calls through video, while those with limited access were contacted by telephone. The control group (CG) will be followed by monthly telephone calls. The intervention will be carried out by 2 trained researchers, scheduled to start in April 2021.

Case managers are responsible for monitoring the volunteers and their families among the intervention proposals to reduce each of the modifiable fall risk factors in the initial assessment. These managers are trained gerontologists who, in addition to having pre-established proposals, hold discussions fortnightly to discuss cases with the entire intervention team, ensuring the best guidelines for volunteers and the alignment of manager´s actions. According to the Brazilian Society of Geriatrics and Gerontology, gerontologists have training in different areas of knowledge (psychology, social work, nutrition, occupational therapy, law, etc), so they are able to plan, coordinate, and evaluate health actions related to older people; in addition, they can deliver biopsychosocial care.

In the first week, for the IG, a multidimensional fall risk assessment will be applied (Multimedia Appendix 2) [10]. In the second session, the case managers will discuss and explain the identified fall risk factors to the participant and his or her caregiver. An individualized intervention proposal based on the identified fall risk factors will be devised considering participants’ preferences and priorities. All IG volunteers will be encouraged to carry out a home-based multicomponent physical exercise program delivered through recorded videos, guidelines, or printed booklets. The exercise program will consist of trunk and lower limb muscle–strengthening, aerobic conditioning, gait, and balance and stretching exercises at moderate intensity, performed twice per week (30-60 minutes per session) with individualized progression every 2 weeks. The exercise program is based on a previous protocol [11] and in line with the recommendations of the American College of Sports Medicine [12], having been adapted for community older adults in the primary health context. Volunteers who agree to participate in the intervention with physical exercises will have to present a medical certificate before carrying out the activities.

In the third session, an individualized intervention plan will be developed with the volunteer and his or her caregiver, taking into consideration priority of the identified fall risk factors, personal preferences, and available resources. During the 16 weeks of the intervention, the case manager, the volunteer, and his or her caregiver will implement the previously agreed plan, which includes recommendations and guidelines, dialogue with suppliers, and referrals for specialized programs. If needed, the plan will be monitored and reviewed by weekly telephone or video calls. During the monitoring, the manager will check if the participant has any difficulty in carrying out the requested activities and will identify what assistance should be offered and what possible changes are needed [5,6]. All cases will be discussed with case managers and 2 specialists in the field. All recommendations, in case of resistance, will be facilitated for better adhesion based on support materials and personal preferences. If there is still refusal, awareness and maintenance of daily risk behaviors will be prioritized so that no accidents happen.

After 16 weeks of the intervention, all volunteers will undergo 6 weeks of detraining (follow-up) in which they will be asked to carry out their usual activities. At the end of the study, all volunteers will receive a booklet of recommendations for reducing fall risk (Figure 1). If positive results are identified, older adults of the CG will be invited to undertake the intervention.

**Figure 1 figure1:**
[figure not shown]
Recommendations for reducing fall risk.

### Outcome Measures

#### Overview

Assessments will be conducted at participants’ homes at baseline, after 16 weeks of the intervention, and at 6 weeks and 1 year post trial completion. The volunteers will be instructed to wear comfortable clothing, closed shoes, not to perform vigorous exercises the day before the assessment, and to wear hearing or visual aids if needed.

Baseline assessments include sociodemographic measures (age, sex, race, marital status, years of schooling, living alone, and income) and general health (BMI; medication use; morbidities; foot problems including dryness of skin, calluses, fissures, open ulcers, and deformities; history of falls, hospitalizations, level of physical activity measured with the Modified Baecke Questionnaire for the Elderly; general health assessed with the Self-Rated Health questionnaire; functional activities evaluated with the Lawton-Brody Scale; and risk of fracture measured with the Fracture Risk Assessment Tool—FRAX).

Primary and secondary outcomes will be reassessed after 16 weeks of the intervention and at the posttrial 6-week follow-up. In addition, after 16 weeks of the intervention, satisfaction and adherence to the intervention will also be assessed among the IG participants. Prospective falls will be collected from baseline to 1-year follow-up. The economic health assessment will be carried out for the period up to the posttrial 1-year follow-up.

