#### Secondary Outcome Measures

Secondary outcomes are falls, physical function (muscle strength of lower limbs, balance, and mobility), mental functions (cognition, depressive symptoms, and fear of falling), fall risk, safety at home, feet and footwear, satisfaction with and adherence to the intervention, and health care costs.

Prospective falls will be collected from baseline to 1-year follow-up using falls calendars and monthly telephone calls. Muscular strength of hip, knee, and ankle joints will be evaluated using the Lafayette dynamometer. In addition, muscle strength, mobility, and balance will be assessed with the Brazilian version of the Short Physical Performance Battery (SPPB). The SPPB consists of 3 tests: Balance Test, Gait Speed Test, and Chair Stand Test [14]. The scores range from 0 to 4, and the total ranges from 0 to 12 points, with higher scores indicating better lower limb function [14]. Balance will also be assessed with the MiniBest test, which has a total score of 28 points, and higher scores indicate better balance [15].

Cognition will be assessed with Addenbrooke’s Cognitive Examination-Revised screening battery, which has a maximum score of 100 points, with a score of ≤78 points indicating cognitive impairment [16]. Digit Span Forward will be used to assess attention and immediate memory deficits (indicated by scores less than 6 points) and Digit Span Backward for measuring attention and working memory deficits (indicated by scores less than 4 points) [17]. To assess depressive symptoms, the Geriatric Depression Scale will be used. Higher scores on this 15-point scale indicate a greater risk of depressive symptoms. The Falls Efficacy Scale-International will be used to assess fear of falling [18]. A total score of ≥23 points is associated with occasional falls, and a score of >31 is associated with recurrent falls [18].

Fall risk will be assessed with the Falls Risk Assessment Tool. The score varies from 0 to 5 points, with a score of 3 or more points indicating a high risk of falls [19]. Regarding home safety, the Home Falls and Accidents Screening Tool will be used. The maximum score is 25 points, and higher scores are indicative of a greater risk of falls and home accidents [20].

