For feet and footwear, the Manchester Foot Pain and Disability Index will be used. A total score of ≥2 points indicate disability associated with foot pain [21]. The tactile sensitivity of feet will be assessed using the 10-gram Semmes-Weinstein monofilament on hallux, the second and fifth metatarsals, 3 points of the forefoot, and 1 point of the midfoot and heel. Flexibility (dorsiflexion and plantar flexion) will be assessed by a goniometer. The characteristics of footwear that the volunteers usually wear at home and when they get up at night will be documented.

After 16 weeks, adherence to the case management program will be assessed by diary entries. Adherence of ≥70% to recommendations will be considered satisfactory [22,23]. In addition, questionnaires will be used to assess reasons for adhering or not adhering to treatment. The prevalence of each recommendation offered in the case management and adherence to these recommendations will also be assessed, using a 3-point scale (total adherence, partial adherence, and nonadherence) [24]. To assess satisfaction of the intervention after 16 weeks, a questionnaire based on the Short Assessment of Patient Satisfaction will be used [25]. A question will be added about the satisfaction of overall care (“How would you rate the health care you received in the past 16 weeks?”), with scores ranging from 0=worst possible care to 10=best possible care.

For economic analyses, the incremental cost effectiveness ratio will be calculated as the difference between the total cost of the IG and that of the CG. Furthermore, the use of health services will be analyzed. The EuroQol-5D is used in many cost-effectiveness studies, which allows the comparison of effects generated by interventions for any disease. Its score ranges from 1 to 3 for each item, allowing 243 different health profiles [26,27].

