### Power and Sample Size

For the primary outcome (fall risk awareness), the sample size was calculated using the G*Power 3.1 software, based on type of study design (2-way ANOVA), type I error of 5%, statistical power of 80%, moderate effect size (0.20), and number of groups (n=2). This revealed that a total sample size of 42 is required. Allowing for 20% dropout, we will recruit a sample size of 60 people.

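### The incremental cost is defined as a difference between arm totals, which moves with the number of people costed; it should be a difference in mean cost per participant, preferably adjusted for baseline hospitalisations.

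*Protocol article*

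**What the plan says.** The formula is in the protocol article, Secondary Outcome Measures, economic paragraph: "the incremental cost effectiveness ratio will be calculated as the difference between the total cost of the IG and that of the CG". The same paragraph adds that "the use of health services will be analyzed" and describes the EuroQol-5D. It names no per-person mean, covariate or interval for cost.

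Four other places bear on it:

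- Health care costs are a secondary outcome ("satisfaction with and adherence to the intervention, and health care costs"), and cost-effectiveness is part of the trial's objective in the Abstract and Discussion.
- The time horizon is long: "The economic health assessment will be carried out for the period up to the posttrial 1-year follow-up".
- The Overview of Outcome Measures lists prior hospitalisations among the baseline data ("history of falls, hospitalizations, level of physical activity"), with no look-back period or unit.
- Randomization and Blinding describes allocation "with a 1:1 allocation using random block sizes" and mentions no stratification.

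Power and Sample Size plans 60 people and allows for 20% dropout. Statistical Analysis states intention to treat and gives no model for costs.

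**The concern.** A sum over an arm grows with the number of people in the sum, so subtracting two sums mixes two things: a difference in cost per person, which is of interest, and a difference in head count, which is not. Costs are to be gathered until a year after the trial ends, and the plan itself expects losses, so unequal numbers with complete costs are likely. Each extra person costed in one arm adds one mean cost to the reported increment even if the intervention changes nothing.

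There is a second, smaller matter. Prior hospitalisation is a plausible predictor of later cost and is already collected. With about 30 people per arm, chance imbalance in it can move the observed cost difference in the one trial that is run. If incremental cost is being defined properly, the same sentence can use this variable.

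At stake is the cost side of a stated objective. The primary outcome is not affected.

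**Working it through.** **Inputs from the article.** Planned sample 60, allocated 1:1, so 30 per arm; dropout allowance 20%; hospitalisations recorded at baseline. The article gives no cost mean, SD or target, so there is no cost figure of the plan's own to reproduce. Its sample size inputs ("type I error of 5%, statistical power of 80%, moderate effect size (0.20), and number of groups (n=2") concern the primary outcome. They give the stated 42 as a repeated measures interaction test if three assessments and a correlation of 0.5 are assumed (power 0.803). They say nothing about costs and serve here only as the source of the arm size.

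**Step 1: arm size.** If mean cost per person is C in both arms, the difference of totals is (n_IG − n_CG) × C and the difference of means is 0.

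- 30 vs 26 costed: 30/26 = 1.15, so totals are about 15% apart. This needs only 4 losses, against the 12 (20% of 60) that the plan allows for.
- 26 vs 22 costed (48 in all, exactly 20% lost): 26/22 = 1.18, about 18% apart.
- 27 vs 21 costed (also 48): difference of totals 6C, difference of means 0.

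How often do such gaps arise? Assume each person is retained independently with probability 0.8. The SD of the difference in numbers is √(2 × 30 × 0.8 × 0.2) = √9.6 = 3.1.

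| Gap in people costed | Probability |
|---|---|
| 2 or more | 0.63 |
| 4 or more | 0.26 |
| 6 or more | 0.07 |

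**Step 2: chance imbalance in prior hospitalisation.** Assume a share p of 0.15, 0.25 or 0.35 hospitalised before entry, and later costs R = 2, 3 or 4 times those of others. For two independent binomials with 30 per arm:

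| | p = 0.15 | p = 0.25 | p = 0.35 |
|---|---|---|---|
| P(imbalance ≥ 10 points) | 0.36 | 0.45 | 0.50 |
| P(imbalance ≥ 20 points) | 0.05 | 0.10 | 0.14 |

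The shift in the unadjusted mean difference, as a share of mean cost, is imbalance × (R − 1) / (1 + p(R − 1)). At exactly 10 points it runs from 0.10 × 1/1.35 = 7% to 0.10 × 3/1.45 = 21%. At exactly 20 points it is twice that, 15% to 41%.

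**Step 3: what adjustment gains.** Those shifts must be set against the total noise. Assume further that the cost SD within each group (hospitalised before or not) is CV times that group's mean, with CV 1 to 2. Taking the non-hospitalised mean as 1:

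- within-group variance W = CV² × [(1 − p) + pR²]
- between-group variance B = p(1 − p)(R − 1)²
- SE of the mean difference = √(2(W + B)/30), divided by the mean 1 + p(R − 1)
- proportional fall in SE on adjustment = 1 − √(W/(W + B))

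Low end (p = 0.15, R = 2, CV = 2): W = 5.8, B = 0.1275. The SE is 55% of mean cost and falls by 1%. High end (p = 0.25, R = 4, CV = 1): W = 4.75, B = 1.6875. The SE is 37% of mean cost and falls by 14%. Over the whole grid the SE is 28-67% of mean cost and the fall is about 1-14%; at CV 2 it is about 1-4%.

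In terms of the correlation r between baseline hospitalisation and later cost, the SE is multiplied by √(1 − r²): a fall of 0.5%, 5%, 13% or 29% for r = 0.1, 0.3, 0.5 or 0.7.

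**The case against.** **The wording may be loose.** The total cost of an arm could be shorthand for all cost components added up and then averaged per person. With 1:1 blocks and intention to treat, the randomised arms will be nearly equal, and if everyone is costed the arm-size effect is close to zero. This stands as a limit on the harm: the effect arises mainly when dropouts' costs are missing and losses are unequal. It does not rescue the sentence, because a formula that is written down should carry the intended meaning, and intention to treat does not supply costs that were never observed.

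**Silence on covariates is not a decision.** A reader might infer that the trial will ignore prior hospitalisations. The article does not say so. It neither includes nor excludes covariates for cost, and an article commonly leaves that choice to a fuller plan. The absence of an adjustment is therefore not an error; the adjustment is offered as an improvement.

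**Chance imbalance is not bias.** A reader might also take the shifts of 7-41% as bias in the planned comparison. They are not. Under randomisation the unadjusted difference in mean cost is unbiased, and chance imbalance is part of the sampling error that an interval covers. The shifts are also conditional on imbalances of a given size. Skewed costs, where a few heavy users dominate, are the setting in which one yes/no covariate helps least. All of this stands.

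**Conclusion.** The point holds for the estimator as written: a difference of arm totals is not a sound incremental cost, because it depends on the number costed. The size is about 15% at 30 vs 26 people with no true difference per person. Gaps of four or more have a probability of about 0.26, assuming independent 80% retention and that those lost are left out of the costing. With complete costing in equal arms the effect is nil.

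Adjustment for baseline hospitalisations is worth having because it is free, but its gain is modest: roughly 1-14% off the standard error, resting on assumed values of p, R and CV that the documents do not supply. The unstated look-back period leaves its predictive strength uncertain. It corrects chance imbalance and improves precision; it does not remove bias.

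The same sentence also calls a cost difference a ratio and names no effect in the denominator. That is a separate defect, and adding a denominator would not repair a numerator built from arm totals.

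**What to change.** In the economic paragraph of Secondary Outcome Measures, define the incremental cost as the difference between arms in mean cost per randomised participant. Estimate it by regressing each participant's total cost on arm and baseline hospitalisations (yes/no or number), and report the adjusted mean difference with a bootstrap 95% interval that resamples participants within arm. Use that figure, in place of the difference of totals, wherever the incremental cost enters. A mean per person removes the mechanical effect of head count but does not fill in costs that are missing for dropouts, so the economic analysis should also state how those are handled.

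The cost is a sentence or two of text and one degree of freedom. It needs no new data and no extra participants. It is best settled before any cost data are analysed.

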#### Primary Outcome Measure

The primary outcome is fall risk awareness and behavior change, which will be assessed using the Falls Risk Awareness Questionnaire (Brazil). A score range from 0 to 32 points and higher scores indicate greater knowledge about fall risk factors [13].

#### Secondary Outcome Measures

Secondary outcomes are falls, physical function (muscle strength of lower limbs, balance, and mobility), mental functions (cognition, depressive symptoms, and fear of falling), fall risk, safety at home, feet and footwear, satisfaction with and adherence to the intervention, and health care costs.

Prospective falls will be collected from baseline to 1-year follow-up using falls calendars and monthly telephone calls. Muscular strength of hip, knee, and ankle joints will be evaluated using the Lafayette dynamometer. In addition, muscle strength, mobility, and balance will be assessed with the Brazilian version of the Short Physical Performance Battery (SPPB). The SPPB consists of 3 tests: Balance Test, Gait Speed Test, and Chair Stand Test [14]. The scores range from 0 to 4, and the total ranges from 0 to 12 points, with higher scores indicating better lower limb function [14]. Balance will also be assessed with the MiniBest test, which has a total score of 28 points, and higher scores indicate better balance [15].

Cognition will be assessed with Addenbrooke’s Cognitive Examination-Revised screening battery, which has a maximum score of 100 points, with a score of ≤78 points indicating cognitive impairment [16]. Digit Span Forward will be used to assess attention and immediate memory deficits (indicated by scores less than 6 points) and Digit Span Backward for measuring attention and working memory deficits (indicated by scores less than 4 points) [17]. To assess depressive symptoms, the Geriatric Depression Scale will be used. Higher scores on this 15-point scale indicate a greater risk of depressive symptoms. The Falls Efficacy Scale-International will be used to assess fear of falling [18]. A total score of ≥23 points is associated with occasional falls, and a score of >31 is associated with recurrent falls [18].

Fall risk will be assessed with the Falls Risk Assessment Tool. The score varies from 0 to 5 points, with a score of 3 or more points indicating a high risk of falls [19]. Regarding home safety, the Home Falls and Accidents Screening Tool will be used. The maximum score is 25 points, and higher scores are indicative of a greater risk of falls and home accidents [20].

For feet and footwear, the Manchester Foot Pain and Disability Index will be used. A total score of ≥2 points indicate disability associated with foot pain [21]. The tactile sensitivity of feet will be assessed using the 10-gram Semmes-Weinstein monofilament on hallux, the second and fifth metatarsals, 3 points of the forefoot, and 1 point of the midfoot and heel. Flexibility (dorsiflexion and plantar flexion) will be assessed by a goniometer. The characteristics of footwear that the volunteers usually wear at home and when they get up at night will be documented.

After 16 weeks, adherence to the case management program will be assessed by diary entries. Adherence of ≥70% to recommendations will be considered satisfactory [22,23]. In addition, questionnaires will be used to assess reasons for adhering or not adhering to treatment. The prevalence of each recommendation offered in the case management and adherence to these recommendations will also be assessed, using a 3-point scale (total adherence, partial adherence, and nonadherence) [24]. To assess satisfaction of the intervention after 16 weeks, a questionnaire based on the Short Assessment of Patient Satisfaction will be used [25]. A question will be added about the satisfaction of overall care (“How would you rate the health care you received in the past 16 weeks?”), with scores ranging from 0=worst possible care to 10=best possible care.

For economic analyses, the incremental cost effectiveness ratio will be calculated as the difference between the total cost of the IG and that of the CG. Furthermore, the use of health services will be analyzed. The EuroQol-5D is used in many cost-effectiveness studies, which allows the comparison of effects generated by interventions for any disease. Its score ranges from 1 to 3 for each item, allowing 243 different health profiles [26,27].

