**Methods:**

Older people with a history of at least 2 falls in the last year will be divided into 2 groups. The intervention group will receive case management at home for reducing the risk of falls, including a multidimensional assessment, explanation of fall risk factors, and elaboration and monitoring of an individualized intervention plan based on the identified fall risk factors, personal preferences, and available resources. The control group will be monitored once a month. Assessments (clinical data, fall risk awareness, physical and mental factors, safety at home, feet and shoes, and risk and rate of falls) will be carried out at baseline, after 16 weeks of the intervention, and at the posttrial 6-week and 1-year follow-up. After 16 weeks of the intervention, satisfaction and adherence to the intervention will also be assessed. Economic health will be evaluated for the period up to the posttrial 1-year follow-up.

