### Statistical Analysis

For statistical analysis, a significance level of 5% will be adopted, and SPSS (version 22.0; IBM Corp) will be used. The analysis will be performed by intention to treat. The Kolmogorov-Smirnov normality test will be applied for all continuous variables to verify data distribution. To compare groups with regard to clinical and sociodemographic characteristics, the chi-square association test and the independent samples *t* test will be used. To test the interaction between groups and assessments, a 2-way, repeated measures ANOVA will be used. If an interaction is identified, simple main effects analyses will be performed, with adjustment for multiple comparisons (Bonferroni correction). To verify which factors influence adherence to the intervention (frequency of ≥70%), a univariate logistic regression analysis will be used. To check which factors influence satisfaction with the intervention, a simple linear regression analysis will be applied.

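### The only between-group outcome model, a group-by-assessment repeated-measures ANOVA, fits fall counts poorly and yields no rate ratio (moderate; secondary outcome)

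*Protocol article*

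**What the plan says.** All references are to the protocol article.

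- **Data.** Under Secondary Outcome Measures: "Prospective falls will be collected from baseline to 1-year follow-up using falls calendars and monthly telephone calls". Falls head the list: "Secondary outcomes are falls, physical function (muscle strength of lower limbs, balance, and mobility".
- **Form of the outcome.** The abstract's Methods paragraph includes "risk and rate of falls" among the assessments made at baseline, 16 weeks, 6 weeks post trial and 1 year.
- **Hypothesis.** The Discussion expects fewer new falls in the intervention group than in the control group.
- **Model.** Under Statistical Analysis: "To test the interaction between groups and assessments, a 2-way, repeated measures ANOVA will be used".
- **Other methods in that section.** Each has its own purpose. Baseline comparison: "To compare groups with regard to clinical and sociodemographic characteristics, the chi-square association test and the independent samples" *t* test. Adherence: "To verify which factors influence adherence to the intervention (frequency of ≥70%), a univariate logistic regression analysis will be used". Satisfaction: "To check which factors influence satisfaction with the intervention, a simple linear regression analysis will be applied". Adherence and satisfaction are assessed in the intervention group only.
- **Analysis set and dropout.** The analysis is by intention to treat. Power and Sample Size allows for 20% dropout.

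**The concern.** Falls in people selected for at least two falls in the past year are event counts, likely to be skewed and overdispersed. They accumulate over time and are not measured at a visit. Two features make exposure uneven: dropout shortens some people's follow-up, and the visits bound intervals of different length (16 weeks, 6 weeks, then up to a year).

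A repeated-measures ANOVA has no exposure term. Someone who leaves early is either excluded, which sits badly with intention to treat, or enters with a short count treated as a full one. The term the plan tests is the interaction, which is not the question for falls. The output is a difference in mean scores, whereas a rate outcome calls for a rate ratio.

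At stake are the efficiency and readability of a hypothesised outcome, and the risk that a different model is chosen after the data are seen.

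**Working it through.** **1. What the plan was sized for.** Stated inputs: effect size 0.20 (read as Cohen's f), alpha 5%, power 80%, two groups. Assumed inputs: m = 3 assessments, correlation 0.5, sphericity. For the within-between interaction:

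- λ = f²·N·m/(1−ρ) = 0.04 × 42 × 3/0.5 = 10.08, with df 2 and (42−2) × 2 = 80
- Power = 0.803, so the stated total of 42 is reproduced.

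The ANOVA was therefore chosen and sized for a score taken at fixed visits. Nothing in the calculation concerns a count or a rate.

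**2. What the interaction tests when applied to falls.** The article gives no fall rate, so take 2 per person-year in controls and a constant rate ratio of 0.5. Use windows of 16, 6 and 52 weeks. (If the year is counted from the end of the intervention, the last window is about 46 weeks.)

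| Window | Control, expected count | Intervention | Difference in counts | Difference in annualised rates |
|---|---|---|---|---|
| 16 wk | 2×16/52 = 0.62 | 0.31 | 0.31 | 1.0 |
| 6 wk | 2×6/52 = 0.23 | 0.12 | 0.12 | 1.0 |
| 52 wk | 2.00 | 1.00 | 1.00 | 1.0 |

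On annualised rates the difference is constant, so the expected interaction is zero although falls are halved. On raw counts an interaction appears only because the windows differ in length.

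**3. Simulation of step 2.** Assumptions: 48 completers (60 × 0.8), full exposure, gamma-Poisson counts with dispersion 1, 1.5 or 2.5 falls per person-year, 600 runs per cell (Monte Carlo error about 1 to 2 points). Rejection rates, lower and higher fall rate:

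| True rate ratio | Interaction, annualised | Interaction, raw counts | Group main effect, raw counts | Negative binomial with offset |
|---|---|---|---|---|
| 1.0 | 5.8%, 6.2% | 6.7%, 9.7% | 5.2%, 6.8% | 7.2%, 7.2% |
| 0.7 | 6.5%, 4.8% | 14.7%, 17.3% | 16.0%, 19.8% | 19.3%, 24.0% |
| 0.5 | 4.3%, 6.3% | 33.2%, 43.0% | 42.2%, 48.7% | 48.2%, 55.3% |

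On annualised rates the interaction rejects at about alpha even when falls are halved. These cells use prospective windows only. Adding the recalled prior-year count as a baseline level would create an interaction, but that count is selected upward by the entry criterion and is not comparable with calendar data.

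**4. Cost of dropping people with partial follow-up.** Assumptions: 30 per arm, 2 falls per person-year, dispersion 1, follow-up scaled to one year, 20% dropout at uniform times in both arms. Mean exposure is 1 − 0.20 × 0.5 = 0.90.

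- *Negative binomial, rate ratio 0.5.* Expected counts are 1.8 and 0.9. SE(log ratio) = √[(1/1.8+1)/30 + (1/0.9+1)/30] = 0.350; z = 0.693/0.350 = 1.98; power ≈ 51%.
- *Completer means, rate ratio 0.5.* 24 per arm, means 2 and 1, variances 2+4 = 6 and 1+1 = 2. SE = √(8/24) = 0.577; z = 1.73; power ≈ 41%.
- *Rate ratio 0.6, same formulas.* About 32% against 27%.

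Simulations agree: 52% to 54% against 40% to 43% at rate ratio 0.5, and 29% to 35% against 23% to 25% at 0.6.

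**5. Precision.** An SE of 0.350 gives a 95% interval of e^(1.96×0.350) ≈ 2.0-fold either way. Falls are an estimation outcome here under any model.

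**The case against.** The strongest reply is that the article never sends falls to the ANOVA. That sentence concerns groups and assessments, falls are logged continuously, and the section is not exhaustive: the cost-effectiveness ratio and health-service use, announced under Secondary Outcome Measures, have no method there either. The model for a secondary count could simply have been left to an analysis plan.

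Part of this stands: the article does not say outright that falls will be analysed by ANOVA. But the abstract lists rate of falls among the visit assessments, and the Outcome Measures overview has secondary outcomes reassessed at visits. On the article's own terms falls therefore come under the group-by-assessment sentence, and no other between-group outcome model is offered. The section commits to one model; it is not silent.

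Three stronger readings are tempting, and the document does not support them.

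- *ANOVA cannot be used on falls at all.* It can be run, and its group main effect on raw counts recovers much of the power (step 3), but the plan makes the interaction the test.
- *Fall risk is equally mishandled.* Secondary Outcome Measures defines fall risk by a visit-based 0–5 score, which can enter the ANOVA. Whether the abstract's wording also means the proportion of fallers is unclear.
- *Dropout alone will create a spurious fall reduction.* With 30% dropout in one arm and 10% in the other, mean exposures are 0.85 and 0.95, a ratio of 0.895, or 11% fewer raw falls with no effect. But the article gives only 20% overall. Equal dropout gives 0.90/0.90 = 1.00, and the artefact also needs truncated counts kept as complete. In a completer analysis of the 30%/10% case with non-informative dropout and no effect, means were 1.98 and 1.99 and type I error was 4.0%.

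**Conclusion.** The point holds at moderate severity. The stated model is a poor one for a hypothesised outcome: it has no person-time, loses people with partial follow-up, tests an interaction that a constant rate reduction barely produces on annualised rates, and yields no rate ratio.

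The efficiency gain from a suitable model is real but modest, about 10 percentage points of power at a rate ratio of 0.5. It rests on assumed fall rate, dispersion and dropout timing, none of which the article gives. Unequal individual follow-up is likewise an inference from the dropout allowance. A small part of the apparent gain may reflect a slightly liberal Wald test (about 6% to 7% at the null with dispersion estimated).

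A reader might infer that the trial's main conclusion is at risk. It is not: the primary outcome is a questionnaire score at fixed visits, and its analysis is untouched.

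**What to change.** Add to Statistical Analysis, before any comparison of falls by group:

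- The number of falls is analysed by negative binomial regression with log(follow-up time) as offset. All randomised participants contribute up to their last calendar or call.
- The proportion with at least one fall is compared by a risk ratio.
- Both are reported with 95% confidence intervals, as secondary and estimation-focused results.
- The repeated-measures ANOVA applies to scores taken at visits, including the Falls Risk Assessment Tool.

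The cost is a few lines of wording. The calendars and monthly calls already supply the data, and the model is available in SPSS (GENLIN). The one downside is the slightly liberal Wald test at this sample size, a further reason to present the interval and not rest on the p-value.
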